##### Qualitative Data Collection

*Observations*. We will conduct observations (40) in eight families in the intervention group. We will mainly participate in home visits and for two of the families also in network meetings with schoolteachers and other stakeholders with focus on the themes mentioned above.

*Interviews*. Interview guides will be inspired by the Theoretical Domains Framework (41). Firstly, we will carry out individual interviews (40) with each of the four intervention coordinators at Liljeborg health camp. The aim is to view the extended maintenance intervention from the perspective of an intervention coordinator covering how they meet a new family, what is on the agenda, how they document their work, and if they feel well equipped to implement the intervention. We will also interview the principal of the Liljeborg health camp as he is a key person in the development and refinement of the extended maintenance intervention.

Four of the eight observed families will be invited for interviews of both child, parent, and affiliated intervention coordinator. The aim of these interviews is to get a more thorough understanding of the different perspectives in the intervention with similarities and differences among the families and intervention coordinators.

##### Qualitative Data Analysis

The qualitative data will be analyzed by the principles of thematic analysis (39) and inspired by principles from collaborative data analysis (42). The collected qualitative data material will be read and discussed thoroughly by the whole research team. The analytic collaboration makes it possible to apply different analytic perspectives and interpretations of the data materials, thereby not one perspective dominates the analytic process.

### Outcomes

The outcomes of the study are summarized in Table 3. The questionnaires are mainly based on measures from the HBSC study (33) which are validated on 11–15 year-old children. They are supplemented with measures from the Danish National Youth Study (DNYS) (43) or already existing questions from DCSH. The items were either transferred directly or adjusted according to the present study population e.g., for bedtimes earlier time options were added. A few items were developed specifically for this study.

**Table 3 T3:** Outcomes.

**Variable**	**Question**	**Item source**	**Data source**	**Time**	**Units/categories**
**Primary outcome**					
Self-reported life satisfaction	*Here is a picture of a ladder. Suppose the top of the ladder represents the best possible life for you and the bottom of the ladder the worst possible life. Where on the ladder do you feel you stand at the present time?*	Cantril ladder, HBSC	All children	– Baseline – Post health camp – Short-term follow up **– Long-term follow up**	0–10
**Secondary outcomes**					
Weight and height (BMI) Objective measures	*What is your weight (in kg)?*	HBSC	All children	Objective measures from the health camps at baseline and post health camp	Kg
	*What is your height without shoes (in cm)?*	HBSC	All children	Objective measures from the health camps at baseline and post health camp	Cm
Weight and height (BMI) Self-reported	*What is your weight (in kg)?*	HBSC	All children	– Baseline – Post health camp – Short-term follow up **– Long-term follow up**	Kg
	*What is your height without shoes (in cm)?*	HBSC	All children	– Baseline – Post health camp – Short-term follow up **– Long-term follow up**	Cm
**Explorative outcomes**					
Parent's report of child's life satisfaction	*Here is a picture of a ladder. Suppose the top of the ladder represents the best possible life for your child and the bottom of the ladder the worst possible life for your child. Where on the ladder do you feel he/she stands at the present time?*	Cantril ladder (modified to parents from HBSC)	Parents	– Baseline – Post health camp – Short-term follow up – Long-term follow up	0–10
Well-being	*Over the last two weeks: I have felt cheerful and in good spirits I have felt calm and relaxed I have felt active and vigorous I woke up feeling fresh and rested My daily life has been filled with things that interest me*	WHO-5(52)	All children	– Baseline – Post health camp – Short-term follow up – Long-term follow up	5 (all the time) to 0 (at no time)
	*In the last 6 months: how often have you had the following…? headache, abdominal pain, backache, feeling low, irritability or bad temper, feeling nervous, difficulties in getting to sleep or feeling dizzy*	HBSC Symptoms checklist	All children	– Baseline – Post health camp – Short-term follow up – Long-term follow up	4 (almost every day) to 0 (never)

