## Methods and Analysis

### Study Setting

#### The Danish Christmas Seal Houses and the Health Camps—A Historical View

In Denmark there is a national focus on childhood overweight and obesity with several initiatives and interventions carried out mainly by volunteers or in municipality settings (23).

Since 1912, DCSH, a private charity foundation in Denmark, has offered sick or vulnerable children a stay at one of their camps. In the early years, focus was on children with tuberculosis, asthma, or other diseases. In the 1960s focus changed to children with overweight and in recent years there has been an increased focus on children with low life satisfaction and social and mental problems. DCSH has thereby adopted the WHO's broad definition of health and includes both physical, social, and mental health in their definition of health among children and adolescents.

DCSH currently runs five health camps in different parts of Denmark. The camps are called Fjordmark, Hobro, Skælskør, Kildemose, and Liljeborg and they offer stays for children from all municipalities in Denmark. The five camps can accommodate between 24 and 48 children at a time with a total of 990 children staying at one of the five camps per year. The children stay at the camp for 10 weeks but return to their homes on the weekends.

The camp accepts children of the age of seven to 14 years (see referral to camp below). Most participating children are between 11 and 14 years old. The distribution of gender is approximately 50/50 with a small overweight of girls. Approximately 5% of the children have a different ethnic background than Danish compared to 11% in the general population. More children attending the health camps have physical or mental problems compared to other children of the same gender and age (24). Compared to other children of the same age, a larger percentage of children attending a health camp live together with parents who have no education or job and/or are divorced or live apart (25). The children struggle with different problems such as low self-esteem, bullying, and/or low life satisfaction. A recent study reveals that 97% of children at the health camps have either overweight or obesity problems (24). Prior to the camp stay, approximately 73% of the children report having a low quality of life (24).

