#### Intervention Group: Extended Maintenance Intervention

The extended maintenance intervention is also delivered by an intervention coordinator who is assigned to a family. Some activities are identical to the standard maintenance intervention such as family day and follow up day along with phone calls (Table 1). The extended maintenance intervention encompasses several new initiatives compared to the standard maintenance intervention. It has a duration of ~16 weeks, 6 weeks while the child is at camp and 10 weeks afterwards. The intervention coordinator will participate in home visits and can also participate in different activities such as school visits and network meetings and assist the family in initiating new sports activities or other relevant activities (Table 2). The number of each of the activities are decided in corporation between the family and the intervention coordinator. The intervention has been in constant development since the beginning of 2018 and it is an ongoing process.

**Table 1 T1:** Main similarities and differences between the two maintenance interventions.

**Family collaboration**	**Standard maintenance intervention (control group)**	**Extended maintenance intervention (intervention group)**
Intervention provider	Intervention coordinator	Intervention coordinator
Duration	9 weeks	16 weeks
Intervention concept	Standard	Tailored to each child
Information day before camp	X	X
Family day during camp	X	X
Follow up day 4 weeks after camp	X	X
Phone call/texts to follow up	X	X
Home visits during and after health camp		X
Network meetings		X
School meetings		X
Meeting with health worker or social worker in home municipality		X
Start-up of sports activities		X

**Table 2 T2:** Activities in the extended maintenance intervention and frequency.

**Activities**	**Number**
**Home visits:** The intervention coordinator visits the child's home and talks to the parents and the child, most often separately. The first visit is while the child is still at camp and therefore solely involves a talk with the parents	2–5
**Network meetings:** The intervention coordinator arranges a meeting with relevant participants e.g., parents, schoolteacher, school principal, social and/or health worker from the municipality etc.	0–2
**School meeting:** The intervention coordinator visits the schools along with the child to tell the classmates about the child's experiences at the camp	0–1

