### Data Collection

#### Data for Effect Evaluation

The data will be collected at the five health camps through questionnaires filled out by both children and parents. The web-based questionnaires are distributed by the DCSH as it is part of their routine data collection. Data are collected at the following time points: (1) Baseline prior to the 10-week health camp, (2) Post health camp on the last day of the health camp, (3) Short-term follow up 3 months after health camp, and (4) Long-term follow up 1 year after completion of camp (primary effect analysis). For both children and parents' questionnaires, existing questionnaires used by the DCSH were expanded by the research group. The parents will receive a reminder by email and eventually by phone if necessary. Data collection and reminders are managed by the DCSH.

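### The explorative symptom checklist has a 6-month recall, so its post-camp and 3-month values mix periods and dilute change; the 1-year value is unaffected

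*Protocol article*

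**What the plan says.** In the protocol article, Table 3 lists the symptom checklist under "Explorative outcomes", for all children. Its stem is "In the last 6 months: how often have you had the following" and its schedule is "Baseline – Post health camp – Short-term follow up – Long-term follow up". WHO-5, in the same well-being block, asks about the last two weeks, and the primary outcome (the Cantril ladder) asks about the present.

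The section Data for Effect Evaluation fixes the timing of the two early forms: "Post health camp on the last day of the health camp" and "Short-term follow up 3 months after health camp". The 1-year form carries the primary effect analysis. Child Questionnaires says that the 3-month form repeats the baseline and 1-year forms apart from a few items on returning home, so the 6-month stem applies there. The same section says that items on the home context are dropped from the post-camp form. It does not mention the checklist.

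The Study Setting section describes the stay: "The children stay at the camp for 10 weeks but return to their homes on the weekends". Of the extended programme the article says: "It has a duration of ~16 weeks, 6 weeks while the child is at camp and 10 weeks afterwards". Data Analysis plans logistic regression for explorative outcomes without naming a time point. The baseline covariates it lists do not include the checklist.

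**The concern.** A recall window longer than the interval between forms makes successive answers describe partly the same weeks. On the last day of camp, a child who answers the question as worded reports mostly on life before camp. At 3 months, about half of the answer concerns time before the return home. Neither value can be read as the child's state at that visit, and a change between forms is measured partly on shared calendar time.

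What is at stake is limited but real. The study asks what happens after the child goes home, and the 3-month form is the first effect questionnaire after the extended programme ends. The checklist is the broadest symptom measure in Table 3, and the Ethical Issues section promises to look for unintended consequences in the quantitative data. An early checklist result close to zero could be taken as evidence of no effect when the window itself has shrunk it.

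**Working it through.** The plan gives no figure on this point, so there is none to reproduce. The check is calendar arithmetic.

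**Inputs**
- Recall window: 6 months (Table 3), taken as 26 weeks.
- Camp: 10 weeks (Study Setting), placed at weeks 0 to 10, with the baseline form at week 0.
- Post-camp form: last day of camp, week 10.
- 3-month form: 13 weeks after camp, week 23.
- 1-year form: 52 weeks after camp, week 62.
- Extended programme: 6 weeks in camp and 10 after, so weeks 4 to 20.
- Standard programme: from 5 weeks into the stay to 4 weeks after it, so weeks 5 to 14.

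**Split of the window.** For a form T weeks after camp ends: weeks after return = min(26, T); camp weeks = min(10, 26 − weeks after return); pre-camp weeks = the rest.

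| Form | Window (weeks) | Pre-camp | Camp | After return |
|---|---|---|---|---|
| Post camp, T = 0 | −16 to 10 | 16/26 = 62% | 10/26 = 38% | 0% |
| 3 months, T = 13 | −3 to 23 | 3/26 = 12% | 10/26 = 38% | 13/26 = 50% |
| 1 year, T = 52 | 36 to 62 | 0% | 0% | 26/26 = 100% |

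**Overlap between forms.** The baseline window is weeks −26 to 0. Post camp shares weeks −16 to 0 with it: 16/26 = 62%. The 3-month form shares weeks −3 to 10 with post camp: 13/26 = 50%.

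**Time since the extended programme began.** At 3 months, weeks 4 to 23 lie inside the window: 19/26 = 73%. The 1-year window opens at week 36, after both programmes have ended (weeks 14 and 20).

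**Variants at 3 months.** With 3 months taken as 12 weeks, 12/26 = 46% is after return. Counting camp weekends as home time gives (13 + 10 × 2/7)/26 = 15.9/26 = 61%.

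**Dilution.** The share of a lasting change that shows equals the recall weight on the weeks since it began. The documents say nothing about weighting, so two assumptions are shown: even weights, and weights falling linearly to zero at 26 weeks. Under the second, the most recent k weeks carry 1 − ((26 − k)/26)².

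| Form and start of change | k | Even | Linear |
|---|---|---|---|
| Post camp, from camp entry | 10 | 38% | 1 − (16/26)² = 62% |
| 3 months, from return home | 13 | 50% | 1 − (13/26)² = 75% |
| 3 months, from start of extended programme | 19 | 73% | 1 − (7/26)² = 93% |

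If children answer only from the last few weeks, all three rows approach 100%.

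**The case against.** The strongest reply is that no stated conclusion rests on these values. The outcome is explorative, the primary effect analysis is at 1 year, and the research questions on 3-month results name life satisfaction, BMI and the intermediate outcomes, not the checklist. Body dissatisfaction, the specific harm named under Ethical Issues, has its own item without a 6-month stem. The ladder and WHO-5 already give near-current readings at every form. All this stands and keeps the point minor. It does not remove it: Table 3 schedules the checklist at all four time points, and nothing shown confines its analysis to 1 year.

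The post-camp part also rests on Table 3 alone. That table still lists school items at post camp, although the text says such items are dropped there, so it is not a sure guide to that form.

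A reader might infer more than the documents support:
- **That both early answers mostly describe time before the return home.** This is true at post camp, but the 3-month split is about even (46% to 61% at home across the variants).
- **That the window hides worsening.** It dilutes improvement equally, and there are no symptom data to fix a direction. At post camp the child has not yet finally returned, so no worsening after return could be missed there.
- **That the comparison is biased.** Both groups have the same window, which by itself only weakens the contrast.
- **That WHO-5 and the checklist must disagree.** They refer to different periods, so they may differ, but this is not shown.

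**Conclusion.** The point holds as a minor one. The 6-month recall is too long for the post-camp and 3-month forms: about 62% of the first window is pre-camp time and about half of the second precedes the return home. Early checklist values mix periods and understate change in either direction.

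For the between-group question at 3 months, even weighting leaves about 50% of a difference that begins on return and about 73% of one that begins with the extended programme. Heavier weight on recent weeks leaves more. These percentages rest on 6 months being 26 weeks, on the baseline form falling at camp start, and on the assumed weighting. The window split needs only the first two.

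The 1-year checklist value is clean, since its window lies wholly after camp and after both programmes. The primary and secondary outcomes are not affected.

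**What to change.** Add a short statement to the analysis plan with three parts:
- Effect inference for the checklist rests on the 1-year form, adjusted for the baseline checklist score in addition to the listed covariates.
- WHO-5 is used for status at post camp and 3 months.
- Any checklist values from those two forms are reported descriptively, with the overlapping recall stated.

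Do not reword the recall period while the study runs. That would break comparability with the study's own baseline form. Protocol Amendment also reports that Liljeborg started the online questionnaires before the other camps, so a change part-way through could reach intervention and control children in different proportions.

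The cost is a few sentences and no new data. The downside is that there is no checklist effect estimate at the two early time points. WHO-5 does not fully replace it, because its items cover mood, energy, rest and interest but not pain or dizziness.

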**Intermediate outcomes**					
Self-efficacy	*How often can you find a solution to problems if you try hard enough?*	HBSC	All children	– Baseline – Post health camp – Short-term follow up – Long-term follow up	5 (always) to 0 (never)
	*How often can you manage the things you decide to do?*	HBSC	All children	– Baseline – Post health camp – Short-term follow up – Long-term follow up	5 (always) to 0 (never)
	*How often are you able to handle unexpected situations?*	Modified from ‘Projekt Optur'(53)	All children	– Baseline – Post health camp – Short-term follow up – Long-term follow up	5 (always) to 0 (never)
Self-esteem	*I like myself*	HBSC	Children 10–14 years	– Baseline – Post health camp – Short-term follow up – Long-term follow up	4 (strongly agree) to 0 (strongly disagree)
	*I am good enough as I am*	HBSC	Children 10–14 years	– Baseline – Post health camp – Short-term follow up – Long-term follow up	4 (strongly agree) to 0 (strongly disagree)
	*Others my age like me*	HBSC	Children 10–14 years	– Baseline – Post health camp – Short-term follow up – Long-term follow up	4 (strongly agree) to 0 (strongly disagree)
Social relations	*How many days a week are you normally with friends in your leisure time outside school or after school care?*	Modified from HBSC	Children 10–14 years	– Baseline – Post health camp – Short-term follow up – Long-term follow up	7 (never) to 0 (7 days a week)
	*How often are you in contact with friend over the internet or on your phone?*	HBSC Modified	Children 10–14 years	– Baseline – Post health camp – Short-term follow up – Long-term follow up	5 (Don't know) to 0 (Almost all the time every day)
	*How often have you been bullied at school in the past couple of months?*	HBSC	All children	– Baseline – Post health camp – Short-term follow up – Long-term follow up	4 (several times a week) to 0 (I have not been bullied at school in the past couple of months)
	*In the past couple of months how often have you been cyberbullied?*	HBSC	Children 10–14 years	– Baseline – Post health camp – Short-term follow up – Long-term follow up	4 (several times a week) to 0 (I have not been cyberbullied in the past couple of months)
	*How easy is it for you to talk to the following persons about things that really bother you?*	HBSC Added answer-categories	All children	– Baseline – Post health camp – Short-term follow up – Long-term follow up	4 (very easy) to 0 (Don't have or see this person)
	*I express my opinion when I think something is unfair*.	HBSC	Children 10–14 years	– Baseline – Post health camp – Short-term follow up – Long-term follow up	3 (almost always) to 0 (almost never)
	*I try to understand my friends when they are sad or angry*.	HBSC	Children 10–14 years	– Baseline – Post health camp – Short-term follow up – Long-term follow up	3 (almost always) to 0 (almost never)
	*I am good at working with others in a group*	HBSC	Children 10–14 years	– Baseline – Post health camp – Short-term follow up – Long-term follow up	3 (almost always) to 0 (almost never)
	*I ask my friends for help when I am in trouble*.	HBSC	Children 10–14 years	– Baseline – Post health camp – Short-term follow up – Long-term follow up	3 (almost always) to 0 (almost never)
Health promoting behavior	*How many times a week do you usually eat or drink…?* • *Fruit* • *Vegetables* • *Candy/chocolate/ chips/ice cream/cake* • *Coke/soda with sugar* • *Fast food (e.g. pizza, kebab, shawarma, burgers, or sausages)*	Combination of HBSC and DCHS	All children	– Baseline – Post health camp – Short-term follow up – Long-term follow up	6 (never) to 0 (every day, more than once)
	*How many times a week do you eat…* • *Healthy breakfast* • *Healthy lunch* • *Dinner with your family*	Combination of HBSC and DCSH	All children	– Baseline – Post health camp – Short-term follow up – Long-term follow up	5 (never) to 0 (every day)
	*When do you normally fall asleep on a school night?*	Developed for study	Children 10–14 years	– Baseline – Post health camp – Short-term follow up – Long-term follow up	8 (20.00 or earlier) to 0 (24.00 or later)
	*When do you usually go to bed if you have to go to school the next morning?*	HBSC Added answer-categories	All children	– Baseline – Post health camp – Short-term follow up – Long-term follow up	8 (20.00 or earlier) to 0 (24.00 or later) Added categories compared to HBSC
	*When do you usually wake up on school mornings?*	HBSC Changed answer-categories	All children	– Baseline – Post health camp – Short-term follow up – Long-term follow up	6 (5.00 or earlier) to 0 (8.00 or later)
	*How many hours a week do you usually exercise so much that you lose your breath or sweat in school or outside school?*	Modified from HBSC	All children	– Baseline – Post health camp – Short-term follow up – Long-term follow up	5 (none) to 0 (7 hours a week or more)
School satisfaction	*Are you happy about your school?*	DCSH	All children	– Baseline – Post health camp – Short-term follow up – Long-term follow up	5 (Yes, always) to 0 (No, never)
	*Do you feel part of the community in your class?*	The Well-being Despite Study(54)	All children	– Baseline – Post health camp – Short-term follow up – Long-term follow up	4 (there is no community in my class) to 0 (always)
	*Most students in my class(es) are kind and helpful*	HBSC	Children 10–14 years	– Baseline – Post health camp – Short-term follow up – Long-term follow up	4 (strongly agree) to 0 (strongly disagree)
	*Other students accept me as I am*	HBSC	Children 10–14 years	– Baseline – Post health camp – Short-term follow up – Long-term follow up	4 (strongly agree) to 0 (strongly disagree)
Body satisfaction	*Are you satisfied with your body?*	Danish Youth Profile(43)	All children	– Baseline – Post health camp – Short-term follow up – Long-term follow up	9 (10 very satisfied) to 0 (1 very dissatisfied)
Parental health promoting behavior	*State how often your family* • *Eat candy, chips, ice cream, cake, or chocolate* • *Eat fast food (e.g. Pizza, kebab, shawarma, burgers, or sausages)* • *Eat fruit* • *Eat vegetables* • *Are observant of portion size* • *Drink coke or soda with sugar*	Modified from HBSC and DCSH	Parents	– Baseline – Post health camp – Short-term follow up – Long-term follow up	6 (never) to 0 (every day, more than once)
	*State how often your family* • *Eat foods marked with whole-grain symbol* • *Eat food with ‘healthier choice' symbol*	Modified from HBSC and DCSH	Parents	– Baseline – Post health camp – Short-term follow up – Long-term follow up	7 (never) to 0 (do not know the symbol)
	*State how often your family* • *Eat breakfast together* • *Eat dinner together*	Modified from HBSC and DCSH	Parents	– Baseline – Post health camp – Short-term follow up – Long-term follow up	5 (never) to 0 (every day)
	*How often do you usually exercise in your free time so much that you get out of breath or sweat?*	Modified from HBSC	Parents	– Baseline – Post health camp – Short-term follow up – Long-term follow up	5 (every day) to 5 (rarely or never)
	*How often does your partner usually exercise in his or her free time so much that he or she get out of breath or sweat?*	Developed for study	Parents	– Baseline – Post health camp – Short-term follow up – Long-term follow up	6 (every day) to 0 (I do not have a partner)
Parental self-efficacy	*How often can you find a solution to your child's problems if you try hard enough?*	Modified from HBSC	Parents	– Baseline – Post health camp – Short-term follow up – Long-term follow up	4 (always) to 0 (never)
	*How often can you handle an unexpected situation your child gets into?*	Modified from ‘Projekt Optur'	Parents	– Baseline – Post health camp – Short-term follow up – Long-term follow up	4 (always) to 0 (never)
